### Interventions

The researchers have been trained in the TEA technique in Pace Translation Medical Research Center, Ningbo, China, and they will teach the patients or their relatives how to implement TEA at home, with the help of a written or electronic user manual. Patients or their relatives can report adverse events by telephone or internet consultation.

#### TEA group

TEA will be performed with a skin electrode patch (50 × 50 mm) accurately placed on bilateral acupoints of Zusanli (ST36) and Neiguan (PC6) based on the theory of traditional Chinese medicine and our previous study [19]. The TEA group will receive TEA 1 h twice daily for 4 weeks, and the parameters of TEA have been well designed for each acupoint: 0.1 s on, 0.4 s off, 100 Hz, 0.25 ms, 2–6 mA at PC6, and 2 s on, 3 s off, 25 Hz, 0.5 ms, 2–6 mA at ST36. The patients will feel mild electric current intermittently but not over the pain threshold, and they are free to perform a slight activity.

#### Sham-TEA group

The sham-TEA group will be performed in the same way except that the acupoints are 15 cm away from accurate acupoints. Ultimately, they will be evaluated for clinical outcomes after interventions for 4 weeks.

### Blinding

The researchers who initially applied or taught the TEA or sham-TEA procedures did not participate in the statistical analysis. The patients and statisticians were blinded to the group assignments. If unblinding happens, the participants will be terminated from the trial immediately, and the data will be marked and not included in the final analysis. The researchers will record the reason in CRFs.

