### Exclusion criteria

Patients who met any of the following criteria were excluded: (1) anastomotic stricture or afferent loop obstruction of the jejunum diagnosed by gastroesophageal radiography, (2) taking drugs such as prokinetics or antidepressant drugs a month prior to surgery or during the trial, (3) severe arrhythmia, (4) tumor recurs during the trial, (5) diabetes mellitus, or (6) mental and physiological illness.

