### Dropout criteria

Patients who choose to quit the study voluntarily or have poor compliance during the trial will be considered as having dropped out. Patients can discontinue the trial if a severe adverse effect occurs, and they can adjust the parameters of TEA slightly if the electric current makes them feel uncomfortable during the TEA procedure.

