### Sample size

Based on a previous electroacupuncture study on gastric emptying function, the response rate is approximately 50–70% [26–30]; however, the data of sham electroacupuncture are insufficient. Thus, we assumed that the response rates of the TEA group and sham-TEA group were 50% and 20%, respectively. Therefore, Δ is 30%. We estimated the sample size using the following formula:
$$ n=\frac{2{\left({\mu}_{\alpha }+{\mu}_{\beta}\right)}^2P\left(1-P\right)}{\Delta ^2} $$

A sample size of 66 patients will give us a power of 90% (*β* = 0.1) with a two-sided significance level of 0.05 (*α* = 0.05). To compensate for a 20% expulsion rate, a total of 90 patients will be required for the study. We will design a ratio of 2:1 (60 patients in the TEA group, 30 patients in the sham-TEA group) based on the response rates of the two groups.

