### Statistical analysis

Sensitivity analysis will be performed to determine the impact of incomplete records on the results. Intent-to-treat analysis of the results will be performed if there is nonadherence or missing data. Only two data statisticians will have access to the final trial dataset, which will only contain coded data, and they will perform statistical analysis using the SPSS version 22.0 software. Student’s *t* test will be performed to assess the difference in the measurements (the residual rates of radioactivity in the stomach at 45, 60, 75, 90, 105, and 120 min) between the TEA group and the sham-TEA group. Paired Student’s *t* test will be used to compare the differences in serum albumin, NE, TNF-α, IL-1β, IL-6, glucose, LF/HF (sympathovagal ratio), and QoL at baseline and 4 weeks after intervention in each group. The *χ*^2^ test will be used for categorical data such as the PG-SGA, HADS, and adverse events. Univariate and multivariate analyses with multiple linear regression will be used to identify independent predictors of outcome measures. The results will be aggregated as median values. *P* values of < 0.05 will be considered as statistically significant.

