### Quality control

To guarantee the quality of the study, all researchers were well trained in the TEA technique, and the patients or their relatives were taught to implement TEA at home, with the help of a written or electronic user manual. Pictures will be taken and uploaded to our database to check the proper acupoints and frequency of TEA each day. Plans to promote participant retention and complete follow-up are as follows: First, online video calls are available for consultation to resolve any technical issues of TEA implementation and to improve research adherence of the patients. Second, we will confirm the completion of TEA each week. Third, the expenses of round trips to the hospital and relevant examinations will be reimbursed to promote participant retention. Fourth, if the participants discontinue or deviate from the trial, we will collect as much data as possible for further analysis. Researchers will be fully apprised of the inclusion and exclusion criteria, and data will be documented in CRFs. A standard operating procedure will be consistently performed according to the study protocol. Drop-outs and their reasons will be recorded. The Medical Ethics Committees will audit the procedure of the trial, have access to these interim results and make the final decision to terminate the trial.

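### Leaving unblinded randomised patients out of the final analysis conflicts with the promised intent-to-treat analysis and can bias the primary comparison

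*Protocol article*

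**What the plan says.** All of these places are in the protocol article.

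- **Blinding:** once a patient is unblinded, "the participants will be terminated from the trial immediately, and the data will be marked and not included in the final analysis". Reasons are to be noted in the case report form.
- **Statistical analysis:** "Intent-to-treat analysis of the results will be performed if there is nonadherence or missing data". A sensitivity analysis for incomplete records is also planned.
- **Quality control:** "if the participants discontinue or deviate from the trial, we will collect as much data as possible for further analysis".
- **Exclusion criteria:** item 2 is "taking drugs such as prokinetics or antidepressant drugs a month prior to surgery or during the trial" and item 4 is "tumor recurs during the trial".
- **Dropout criteria:** "Patients who choose to quit the study voluntarily or have poor compliance during the trial will be considered as having dropped out".
- **Sample size:** "To compensate for a 20% expulsion rate, a total of 90 patients will be required for the study". The assumed response rates are 50% (TEA) and 20% (sham-TEA), with 60 and 30 patients.

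**The concern.** The Blinding rule removes randomised patients from the final analysis itself, not from a secondary per-protocol set, because of something that happens after randomisation. That is safe only if the event is unrelated to both arm and outcome, and nothing in this design ensures that. The sham differs from TEA only in electrode site, displaced by 15 cm. Patients or relatives apply the device at home, and photographs are taken each day to check placement. A patient could learn the allocation from the electrode site, from a perceived effect or its absence, or from an adverse event. If those removed differ between arms in their chance of responding, the groups compared are no longer the groups randomised.

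The sham arm has only 30 patients, so a few removals there matter. If termination also ends outcome collection, the missing values cannot be recovered at the analysis stage.

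**Working it through.** **1. Blinding against Statistical analysis.** Take one randomised patient who becomes unblinded at week 2. Under Blinding, the patient is terminated and left out of the final analysis. Under Statistical analysis, intent-to-treat applies if there is nonadherence or missing data. Immediate termination before the 4-week assessment produces missing data, so the condition is met and the patient belongs in the analysis. Both instructions cannot be carried out for this patient.

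**2. Exclusion criteria against Statistical analysis.** Recurrence in the course of the trial cannot be known at enrolment, and the drug-use item reaches past enrolment too. The text does not say whether a randomised patient who meets either item later stays in the analysis. This is an ambiguity, not a stated removal.

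**3. The plan's own figures.** The Sample size section gives 66 evaluable patients for 90% power at two-sided 0.05. Its formula with P = 0.35 gives 53.1 per arm, so 54 per arm after rounding up, and 66 is not reproduced. That is a separate matter, and nothing here depends on it. The 20% allowance on 90 is 18 patients, leaving 72, or 48:24 if the loss is even.

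**4. Power if patients are lost evenly (the loss shares are assumptions, except that 20% is the plan's total allowance).** Inputs: p₁ = 0.50, p₂ = 0.20, two-sided 0.05, z = 1.960.

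Power = Φ[(0.30 − 1.960·se₀)/se₁], where se₀ = √[p̄(1−p̄)(1/n₁+1/n₂)], se₁ = √[0.25/n₁ + 0.16/n₂], and p̄ = 0.40 at 2:1.

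- 60:30: se₀ = √(0.24 × 0.05) = 0.1095; se₁ = √0.0095 = 0.0975; (0.30 − 0.2147)/0.0975 = 0.875; power 80.9%.
- 48:24: se₀ = √(0.24 × 0.0625) = 0.1225; se₁ = √0.011875 = 0.1090; (0.30 − 0.2400)/0.1090 = 0.550; power 70.9%.
- In between, a 5% even loss gives 78.7% and a 10% even loss gives 76.3%.

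**5. Hypothetical selective removal.** The document gives no frequency or cause of unblinding, so these figures show only that the result can move either way. Start from 30/60 and 6/30, a difference of 30 points, and remove 10% of one arm.

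| Removed | Rates then analysed | Apparent difference |
|---|---|---|
| 6 TEA non-responders | 30/54 vs 6/30 | 35.6 points |
| 6 TEA responders | 24/54 vs 6/30 | 24.4 points |
| 3 sham non-responders | 30/60 vs 6/27 | 27.8 points |
| 3 sham responders | 30/60 vs 3/27 | 38.9 points |

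With no true effect and an assumed 50% response in both arms, removing 6 TEA non-responders gives 30/54 against 15/30. That is a false difference of 5.6 points, with two-sided rejection of about 7.8%. Removing 12 gives 30/48, a false difference of 12.5 points and rejection of about 19%.

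**The case against.** The other side has several fair points.

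- **Exclusion criteria.** A reader might infer that these also order the removal of data after recurrence or drug use. They do not say so. They can be read as eligibility and concomitant-drug restrictions, with later deviations handled under intent-to-treat and the sensitivity analysis. This stands, so the limb is secondary.
- **Quality control.** A reader might infer that the promise to collect data after deviations contradicts Blinding. It does not strictly do so. Blinding has the data marked rather than destroyed, and marked data could serve further analysis in a sensitivity set. The firm conflict is between Blinding and Statistical analysis.
- **Wording of the intent-to-treat sentence.** Unblinding is in itself neither nonadherence nor missing data. That is true, but the termination that the same sentence orders creates missing data, so the conflict remains.
- **Bias.** A reader might infer that the trial will be biased in a known direction. The document does not support this. It gives no causes or rates of unblinding, and its limitations paragraph says that most patients with delayed emptying have no specific symptoms. That weakens the idea that patients would sense success or failure, or start a prokinetic because of it. Only the possibility of bias stands.
- **Prokinetics.** These act on gastric emptying, which is the primary endpoint. Statisticians may reasonably differ on how an outcome measured after such use should count. Keeping the patient in the intent-to-treat set does not settle that question.

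**Conclusion.** The point holds for the Blinding rule. It is an explicit instruction to leave randomised patients out of the final analysis, it conflicts with the intent-to-treat promise, and an analysis plan could repair it only by contradicting the protocol. It can bias the primary comparison, with direction and size unknown. Every selective-removal figure above is hypothetical.

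The loss of precision is clearer but also conditional. Power falls from about 81% to about 71% if 20% are lost evenly, with response rates of 50% and 20%. The document does not say how much of its 20% allowance is due to unblinding, so the rule's own share could be much smaller.

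The Exclusion criteria are an ambiguity to be reconciled, not proof of further removals.

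**What to change.** 1. In Blinding, delete the instruction that unblinded patients' data are left out. State that their outcomes continue to be collected and that they are analysed in the arm assigned, in line with Statistical analysis and Quality control. Keep recording the fact and reason of unblinding.
2. Show the analysis without unblinded patients only as a labelled sensitivity analysis.
3. Limit the Exclusion criteria to facts known before randomisation. State that later recurrence or drug use does not remove a patient from the intent-to-treat set. How outcomes after drug use are counted can be set out in the analysis plan.

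Whether such patients continue treatment is a clinical matter and is not addressed here.

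The cost is a protocol amendment, a few extra outcome visits, and an estimate that may be somewhat diluted. The article reports recruitment as ongoing, so the change could be made before analysis. Outcomes of patients already terminated should be sought where consent allows.

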### Participant timeline

Enrollment and allocation will be conducted before the study. TEA or sham-TEA intervention will be given twice daily from week 1 to week 4. The patients’ gastric emptying function, nutritional status, and quality of life (QoL) will be assessed 1 year after the treatment as a follow-up. The schedule of enrollment, allocation, postallocation, and close-out is shown in Fig. 1.

### Outcome measures

#### Primary outcome measures

##### Gastric emptying function

We will evaluate the gastric emptying function of these postoperative patients who visit outpatient clinics. Gastric scintigraphy will help us to evaluate the gastric emptying function and has the advantages of being noninvasive and painless. ^99m^Tc tin colloid will be mixed with a semisolid diet of 200 g of rice gruel with a boiled egg. Radioactive signs will be recorded from diet intake to 120 min afterward, and the residual rates of radioactivity in the stomach at 45, 60, 75, 90, 105, and 120 min will be calculated by a half-life of 9 mTc. We will compare the recorded residual rates and the time to 50% residual rate between the two groups as the primary outcomes.

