**Methods:**

A total of 90 eligible participants who underwent distal gastrectomy will be randomly allocated to either the TEA group (*n* = 60) or the sham transcutaneous electroacupuncture (sham-TEA) group (*n* = 30). Each participant will receive TEA on the bilateral acupoints of Zusanli (ST36) and Neiguan (PC6) for 4 weeks. The primary outcomes will be the residual rates of radioactivity in the stomach by gastric scintigraphy and total response rates. The secondary outcomes will be endoscopic features, autonomic function, nutritional and psychological status, serum examination, and quality of life (QoL). The adverse events will also be reported. The patients will be followed up 1 year after the treatment.

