##### Total response rates

We will compare the total response rates between the two groups. Meanwhile, we will perform a subgroup analysis by different operation types of Billroth-I, Billroth-II, or Roux-en-Y reconstruction. In fact, some researchers reported that Roux-en-Y reconstruction could destroy the natural small-bowel pacemaker [20–22]. Subgroup analysis of laparoscopic and open surgery will also be included in our results.

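### Eight primary comparisons share one unadjusted P < 0.05 threshold, with no deciding outcome, testing order or success rule

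*Protocol article*

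**What the plan says.** The abstract of the protocol article names two kinds of primary outcome: "The primary outcomes will be the residual rates of radioactivity in the stomach by gastric scintigraphy and total response rates". The section Gastric emptying function expands the first kind. There, "the residual rates of radioactivity in the stomach at 45, 60, 75, 90, 105, and 120 min will be calculated", and then: "We will compare the recorded residual rates and the time to 50% residual rate between the two groups as the primary outcomes". The next section, Total response rates, stands under the same Primary outcome measures heading and adds: "We will compare the total response rates between the two groups".

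The Statistical analysis section assigns Student's t test to the residual rates at the six listed times. It names no joint or repeated-measures test of the curve. It names no specific test for half-emptying time or for the response rate, which fall under the general rule that P "values of < 0.05 will be considered as statistically significant".

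The Sample size section uses the response rate only (50% versus 20%). It claims "A sample size of 66 patients will give us a power of 90" per cent, "with a two-sided significance level of 0.05", and no part of that 0.05 is set aside for another primary outcome.

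On timing, the Sham-TEA group section speaks of evaluation after 4 weeks of intervention. The Participant timeline adds a second assessment of gastric emptying 1 year after treatment. Neither primary-outcome section says which time is primary.

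**The concern.** A trial with several primary comparisons needs a rule that turns their results into one conclusion: one outcome decides, or all must succeed, or any may succeed with alpha shared or ordered among them. None is given here. A report could therefore present a single significant time point, say the residual rate at 90 min, as a positive primary result, and the text would not forbid it. The 5% error rate used in the sample size would then not describe the trial's main claim. The response rate, which is the only outcome the trial was sized on, would carry no more weight than any of the other seven.

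**Working it through.** **Count of comparisons.** Six residual rates (45, 60, 75, 90, 105, 120 min) + time to 50% residual + total response rate = 8. If the 1-year scintigraphy were also read as primary, the count would be higher.

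**The plan's own error figure.** The only alpha stated is 0.05, two-sided. The documents give no familywise figure, so there is none to reproduce.

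**Independent tests, any one counting as success.** 1 − (1 − 0.05)^8 = 1 − 0.663 = 0.337, or 34%. The Bonferroni upper bound is 8 × 0.05 = 40%.

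**Correlated tests.** The residual rates come from one scan at 15-minute steps, so independence is unrealistic. The documents give no correlations, so a range was assumed. Trials with no treatment effect were simulated at 48:24 or 60:30. The six residual rates had correlation ρ between neighbours, falling off with distance. Half-emptying time was correlated 0.5 to 0.95 with the mean residual rate, and response was a binary measure tied to the same curve. The chance of at least one P < 0.05 among the eight was:

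| Assumed ρ between adjacent times | At least one of eight |
|---|---|
| 0.6 | about 25-27% |
| 0.7 | 22-25% |
| 0.8 | 20-23% |
| 0.9 | 16-20% |
| 0.95 | 14-17% |
| 0.98 | about 10-15% |
| independent | 34% |

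The spread within a row reflects how closely half-emptying time and response follow the curve. As a cross-check, eight equally correlated z tests give 25% at correlation 0.5, 16% at 0.8 and 10% at 0.95.

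**Adjusting across all eight instead.** 0.05/8 = 0.00625 per test. For 50% versus 20%, response-rate power would be 50% at 60:30 and 37% at 48:24, and 183 evaluable patients would be needed for 90% power at 2:1.

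**Keeping one primary at 0.05.** The power of the response rate matters here, so the plan's figure was checked first. P is not defined next to the formula. Taking it as the mean, (0.50 + 0.20)/2 = 0.35:

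n = 2 × (1.960 + 1.282)² × 0.35 × 0.65 / 0.30² = 53.1 per group, about 106 in total.

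The stated 66 is not reproduced. For the actual 2:1 design the pooled rate is (2 × 0.50 + 0.20)/3 = 0.40, and power = Φ[(0.30 − 1.960 × SE0)/SE1], where SE0 = √[0.40 × 0.60 × (1/n1 + 1/n2)] and SE1 = √[0.25/n1 + 0.16/n2]:

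- 60:30: SE0 = 0.1095, SE1 = 0.0975, power 81%.
- 48:24 (90 × 0.8 = 72 after the planned 20% loss): SE0 = 0.1225, SE1 = 0.1090, power 71%.
- 44:22 (66 patients): power 67%.

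**The case against.** Four objections deserve an answer.

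First, testing order and adjustment often sit in a statistical analysis plan that is not shown. That would answer a complaint that an adjustment method is missing. It does not answer this point, because the article itself names eight primary comparisons and sets one general threshold. Which outcome is primary is a protocol decision.

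Second, no sentence says that any one significant result counts as success. This stands. If all eight had to succeed, there would be no inflation. The text neither adopts nor excludes either rule, so the inflation is a possibility left open. A reader might infer that the trial's false-positive rate simply is some figure such as 15-27%. The documents do not support that: the size depends on assumed correlations and on the any-one-wins reading, and very high correlation takes it to about 10%.

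Third, the abstract could be read as two outcomes rather than eight. Even two independent tests at 0.05 give 1 − 0.95² = 9.75%, and half-emptying time plus response alone gave 7-9% in the simulations. The t tests are also listed time by time, so the six do not collapse into one.

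Fourth, two further inferences go too far. The subgroup analyses by reconstruction type and by surgical approach appear under the primary heading, but the text never calls them primary. That is a matter of placement and adds nothing to the eight. Nor do the documents show that a response cut-off would be picked after the results are seen. They leave response undefined, and they also say that the statisticians are blinded to group.

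**Conclusion.** The point holds. The protocol fixes eight primary between-group comparisons under one blanket P < 0.05, gives no way to combine them, and sizes the trial as though the response rate were the only one.

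If any one significant result may be claimed, the false-positive rate is above 5% at every correlation examined: about 10-27% for adjacent correlations of 0.98 down to 0.6, and 34% under independence. The lower end already doubles the nominal rate. The count of eight and the single threshold are read directly from the text. The percentages are assumption-based and should be reported as such. The defect concerns the main claim and should be corrected before unblinding.

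**What to change.** Amend the protocol and the registry entry before the data are unblinded. The article reports recruitment as ongoing and no data to date.

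1. Name one primary outcome at one time, the end of the 4-week treatment. The response rate is the natural choice because it sized the trial. Test it once at two-sided 0.05.
2. Fix the scintigraphic definition of response in advance. The entry criterion, half-emptying time above 70 min, offers one candidate: no longer above that value at 4 weeks. Nothing in the documents ties it to the assumed 50% and 20%. Since every patient enters above the threshold, a small shift or regression to the mean could count as response and raise the sham rate. The sponsor should check any definition against those two rates before adopting it.
3. Make half-emptying time and one overall test of the residual curve key secondary outcomes, tested in that order, each only if the preceding test is significant.
4. Label the subgroup analyses exploratory and move them out of the primary heading.

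The cost in wording is small and no patients are added for multiplicity. There are two real downsides. A single residual-rate time point can no longer carry a positive claim. The trial would also rest on a binary endpoint with about 71% power at 48:24 and 81% at 60:30, not 90%, so the sample size needs separate attention. If the sponsor prefers half-emptying time as the single primary outcome, that controls the error equally well but needs its own sample-size basis.
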